11.8 Plan for report of harmful cases

Reports of serious adverse events (airway-related problems such as hypoxic brain damage, hypoxic organ damage et etc.) and unexpected problems and research-related adverse events are reported to the IRB within 7 days, and within 24 hours for serious and unexpected adverse events.

11.9 Data Safety Monitoring Plan (DSMP)

Principal investigator will make comparisons between the source documents and the study protocol at every 6 months to assure the completeness of data and will review the safety data of subjects. The subject identification code on the data will be encoded, and will be filed in a safe installed with a locking device while the electronic document will be saved in a computer which is restricted for access.

**12. Statistical analysis**

Both intention-to-treat and per-protocol analyses will be performed and missing data will be imputed with the last observation carried forward value. Continuous variables

will be presented as mean and standard deviation or median and interquartile range according to the Kolmogorov-Smirnov test, and categorical variables as number of patients and proportion.

The incidence of postoperative sore throat (primary outcome)

will be compared with a noninferiority analysis.The noninferiority of the nonpretreated tube over the water-lubricated tube will be accepted if the upper bound of a 95% confidence interval is below the predetermined noninferiority margin of 15%. For secondary outcomes, continuous variables will be compared with an independent t test or the Mann-Whitney U test and categorical variables with Pearson’s chi-squared test or Fisher’s exact test.

All tests are two-sided and P < 0.05 is considered statistically significant. A statistician not involved in data collection will conduct all statistical analyses using SPSS software (version 21.0, SPSS Inc., IBM, Chicago, IL, USA).

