10.2 Exclusion criteria

- Symptoms of sore throat, hoarseness, and respiratory infections as assessed by a study

investigator at baseline

- Gastroesophageal reflux diseases defined by history taking from patients

- Congenital or acquired abnormalities of the upper airway

- Previous airway surgeries

- Previous history of aspiration

- Coagulation disorders

- History of difficult intubation or conditions with an expected difficult airway including Mallampati classification ≥3 or a thyromental distance <6.5 cm

- Use of airway instruments other than a direct laryngoscope such as a fiberoptic bronchoscope,

video laryngoscope, or lighted stylet

- Anticipated nasotracheal intubation or insertion of a nasogastric tube

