10.3 Sample size calculation

The primary outcome of this trial is the incidence of postoperative sore throat within 24 h after surgery. Assuming the incidence of 57% in a previous study, 135 patients are required in each group to obtain 80% statistical power, 5% risk of type-I error, and 15% noninferiority margin. The margin was determined based on our clinical judgment that the incidence of postoperative sore throat is relatively high (50–60%), so the difference within 15% in the incidence would be considered clinically noninferior. Considering 10% dropout, the estimated sample size is 300 in both groups. The sample size is calculated using a PASS software (version 11.0, NCSS, Kaysville, UT, USA).

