concentration of desflurane to obtain a bispectral index (A2000 XP, Aspect Medical Systems, Newton, MA, USA) value of less than 60, and total fresh gas flow is supplied at 2 L/min throughout the operation.

At the end of surgery, reversal agents are administered to antagonize the neuromuscular blockade. After gently suctioning the oral secretions from the oropharynx, extubation is carefully performed at a train-of-four ratio above 90% when the participants are able to achieve spontaneous breathing and obey verbal commands. Extubation time is defined as the interval from cessation of anesthesia until extubation. After extubation, the presence of blood on the tube surface or in the oral cavity is examined. An investigator blinded to the group assignment evaluates patient-reported sore throat at 0, 2, 4, and 24 h after surgery.

[figure not shown]

The investigator also examines oropharyngeal injuries via direct inspection using a penlight and tongue depressor with regard to the location (posterior pharyngeal wall, uvula, tonsillar fossa, pillar, or others) and type (hyperemia, edema, hematoma, or others) at 2 and 24 h after surgery. The amount of intraoperative and postoperative analgesic drugs is checked until 24 h after surgery.

At 7 days after surgery, the investigator also asks about the symptoms of respiratory infections, such as cough, sputum, rhinorrhea, sore throat, or fever, and whether the patients have been diagnosed with a common cold, tonsillitis, pneumonia, or any other respiratory infectious diseases and prescribed related medications postoperatively. If the patients have been discharged from hospital, they are contacted by telephone and asked about respiratory infections.

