11.5 Primary outcome measurements

- Incidence of sore throat during postoperative 24 h

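### Last observation carried forward does not suit an any-sore-throat-in-24-h outcome: it cannot recover an unobserved first event, and with similar loss in both arms it leans modestly towards noninferiority

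*Protocol*

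**What the plan says.** Section 12 gives one missing-data rule, in the same sentence as the intention-to-treat and per-protocol analyses: "missing data will be imputed with the last observation carried forward value". It names no exception and no sensitivity analysis.

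Section 10.3 defines the primary outcome: "The primary outcome of this trial is the incidence of postoperative sore throat within 24 h after surgery". Section 11.5 repeats it as "Incidence of sore throat during postoperative 24 h". Under Section 11.1 a blinded investigator "evaluates patient-reported sore throat at 0, 2, 4, and 24 h after surgery". The outcome is therefore positive if any of four assessments is positive.

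Section 12 accepts noninferiority of the dry tube if the upper 95% confidence limit for the difference lies below 15 percentage points. Section 11.7 lists drop-outs, including a change of airway device and failure to extubate, that can arise before the first assessment. Section 10.3 allows for 10% dropout.

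**The concern.** Carrying the last value forward is a rule for a status at a fixed time. Here the outcome accumulates over time. Once a sore throat is recorded, the patient is an event and imputation is irrelevant. If none has been recorded, the rule carries a negative forward and the patient counts as event-free, although a sore throat may have begun after the last assessment.

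For patients with no postoperative assessment there is nothing after intubation to carry forward. The only earlier status is the eligibility screen, which excludes patients with "Symptoms of sore throat, hoarseness, and respiratory infections as assessed by a study" investigator at baseline. Either the rule gives these patients no value, and the intention-to-treat analysis is undefined for them, or it scores them from a status that predates the exposure.

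In a noninferiority trial the direction matters. Scaling both incidences down by a similar factor pulls a true difference towards zero, and so makes a wrong claim of noninferiority more likely.

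**Working it through.** **The plan's own figure.** Section 10.3 says "Assuming the incidence of 57% in a previous study, 135 patients are required in each group", with "80% statistical power, 5% risk of type-I error, and 15% noninferiority margin". For equal true rates, n = (z₁₋α + z_power)² × 2p(1−p) / margin². With a one-sided α of 5%: (1.645 + 0.842)² × 2 × 0.57 × 0.43 / 0.15² = 6.18 × 0.4902 / 0.0225 ≈ 135. Dropout: 135 / 0.90 = 150 per arm, 300 in total. The figure reproduces. (With a one-sided 2.5% it would be 172.)

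**What the rule does to the outcome.** Each of four assessments can be yes, no or missing: 3⁴ = 81 patterns, of which 2⁴ = 16 are complete and 65 incomplete. Applying the rule to the 65:

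- 34 missing cells become yes, 34 become no, and 40 stay undefined because nothing precedes them.
- The any-sore-throat result changes in 0 of 65 patterns.

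The rule therefore recovers no event. Its only effect on the primary outcome is to keep incompletely observed negatives in the denominator as non-events.

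**Effect on the error rate.** Inputs:

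- Saline incidence 57% (Section 10.3). Dry incidence 57% + 15 = 72%, the boundary at which noninferiority just fails.
- 150 per arm (Section 11.2).
- Two-sided 95% interval, hence nominal 2.5%. Section 12 says that all tests are two-sided. The unpooled Wald form is my assumption.
- m = share of an arm with missing data. The 10% dropout is from Section 10.3; its split by arm is assumed.
- s = share of the missing patients' true events that goes unobserved. The protocol does not give it, so a range is shown. Missing patients are assumed to have the same true incidence as the others.

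Recorded incidence = true incidence × (1 − m·s). With equal loss, recorded difference = 15 × (1 − m·s) points. The error rate is the exact binomial probability, at the recorded incidences, that d − c + 1.96 √[d(1−d)/150 + c(1−c)/150] < 0.15, where d and c are the observed dry and saline proportions.

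| Loss dry / saline | s | Recorded dry / saline | Difference (points) | False noninferiority |
|---|---|---|---|---|
| none | – | 72.0% / 57.0% | 15.0 | 2.5% |
| 10% / 10% | 0.10 | 71.3% / 56.4% | 14.85 | 2.7% |
| 10% / 10% | 0.25 | 70.2% / 55.6% | 14.6 | 2.9% |
| 10% / 10% | 0.50 | 68.4% / 54.2% | 14.25 | 3.3% |
| 10% / 10% | 1 | 64.8% / 51.3% | 13.5 | 4.2% |
| 12% / 8% | 1 | 63.4% / 52.4% | 10.9 | 10.3% |
| 8% / 12% | 1 | 66.2% / 50.2% | 16.1 | 1.5% |

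For comparison, analysing only complete patients (135 per arm, missing at random) gives 2.4%. If the 95% limit were read as one-sided, matching the 5% behind the sample size, the error is 4.8% with no loss. With equal 10% loss it is 5.5%, 6.3% and 8.3% for s = 0.25, 0.50 and 1.

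**The case against.** The strongest defence is that the harm is small under the plan's own dropout. Patients who miss only a late assessment have often declared a sore throat already, or would not develop one, so s may be well below 1. With equal 10% loss and s = 0.10 the rate is 2.7%. The planned per-protocol analysis may also drop the Section 11.7 patients and so remove those with no assessment. Both arguments stand as mitigation. They do not cure the problem: the protocol does not define the per-protocol set, does not say which analysis governs the claim, and applies the rule in the sentence that introduces both.

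Three stronger readings are tempting, and the documents do not support them.

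- A reader might infer that every missing assessment becomes a negative. It does not: an earlier positive is carried forward as positive, and that patient is already an event.
- A reader might infer that the plan imputes the baseline negative for patients never assessed. Section 12 does not say that the eligibility screen counts as an observation, and Section 11.4 lists sore throat only at 0, 2, 4 and 24 h. Nor does Section 11.7 say when each drop-out occurs or that data collection then stops.
- A reader might infer that the rule always inflates the error, perhaps severely. With 15% dry/5% saline loss and all events lost the rate is 27.9%, but the mirror case gives 0.2%. Differential loss is conceivable, because a change of device follows failed attempts with the allocated tube, but nothing in the protocol says which arm would lose more.

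**Conclusion.** The concern holds as a moderate point. The protocol itself fixes a rule that does not fit its primary outcome, so this is not a detail left to a statistical analysis plan. The rule cannot recover an unobserved first event, and it gives no defensible value for a patient without a postoperative assessment.

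With similar loss in both arms and a truly worse dry tube, the bias favours noninferiority. At the planned 10% dropout it raises a nominal 2.5% error to about 2.9–3.3% if a quarter to a half of the missing patients' events are lost, and to 4.2% if all are. These sizes rest on an assumed s, on equal loss, and on missing patients resembling the others. With unequal loss the direction depends on which arm loses more, so neither a large inflation nor a uniform direction can be claimed.

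**What to change.** In Section 12, remove the carry-forward rule for the primary outcome and state:

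1. Any positive assessment at 0, 2, 4 or 24 h makes the patient an event.
2. For patients with incomplete data and no positive assessment, including those never assessed, use multiple imputation by arm from the available time points and from baseline and intubation variables.
3. Add a tipping-point analysis in the direction conservative for noninferiority: raise the assumed sore-throat rate among missing dry-arm patients relative to missing saline-arm patients until the conclusion changes, and report that point.

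A tipping-point analysis is preferable to counting every missing dry-arm patient as an event. At equal true rates of 57% and 10% missing per arm, that rule would record 0.9 × 57 + 10 = 61.3% in the dry arm, a spurious difference of 4.3 points. By normal approximation, power at 150 per arm would fall from about 75% to about 47%.

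The cost is revised wording, a little more analysis work and a slightly wider confidence interval. As a guide, at a true difference of zero, power is 71.0% with 135 complete patients per arm, against 73.7% under carry-forward with 10% loss and all missing patients' events lost.
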